### Patient public involvement {8a}

The Principle Investigator (PI) will regularly meet with the researchers and students involved in the study on a weekly basis and with the PIs of the projects under CIDEFES every 2 weeks. During these meetings, senior researchers will discuss the main issues of SUFHA and how experiences and proposals from participants should be taken into consideration during the decision-making process for final intervention refinement. As this is a low-contact intervention, we did not consider other participatory research design methods.

## Methods: participants, interventions, and outcomes

### Study setting {9}

Office-based workers will be recruited via university advertisements (e.g., posters, banners, invitation emails). The ones interested and fulfilling the inclusion criteria will be contacted to participate in the trial with sit-stand desks at work and their experiences on barriers and facilitators of use collected (via focus group) to delve deeper into their motivations or doubts related to the study. A website was created so that the participants can have more detail on the RCT itself, evaluations, expectations, and a tool for disseminating strategies to prompt participants to use the sit-stand desk throughout the intervention (https://sufha.ulusofona.pt).

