**Methods:**

A two-arm (1:1), superiority parallel-group cluster RCT will be conducted to evaluate the effectiveness of this intervention in a sample of office-based workers from a university in Portugal. The intervention will consist of a psychoeducation session, motivational prompts, and contextual modification promoted by a sit-stand desk in the workplace for 6 months. The control group will work as usual in their workplace, with no contextual change or prompts during the 6-month intervention. Three assessment points will be conducted in both groups, pre-intervention (baseline), post-intervention, and a 3-month follow-up. The primary outcomes include sedentary and physical activity-related variables, which will be objectively assessed with 24 h monitoring using the ActivPAL for 7 days. The secondary outcomes include (a) biometric indices as body composition, body mass index, waist circumference, and postural inequalities; and (b) psychosocial variables such as overall and work-related fatigue, overall discomfort, life/work satisfaction, quality of life, and eating behavior. Both the primary and secondary outcomes will be assessed at each assessment point.

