### Who will take informed consent? {26a}

The PI of the study will contact all potential participants for a detailed explanation of the trial, as well as provide the link to the website of the study, so that all doubts can be solved prior to the baseline evaluation moment. On the previous day to the baseline measurement, each potential participant will receive an email with informed consent, allowing access to all the corresponding information in advance. On the next day (baseline assessment), one trained evaluator (i.e., Ph.D. candidate with a Master in Exercise and Health and a certified Exercise Physiologist by the Portuguese Government) will answer any questions prior to the potential participants signing the written informed consent.

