There is evidence that temporary context changes, such as holidays, threaten to derail newfound routines, such as standing more often in the workplace [39]. Furthermore, after the intervention period, participants will no longer have the sit-stand desk. Thus, to enhance motivation and self-regulation for internalizing the new routines of breaking up sitting time, intervention participants will also be provided motivational nudges throughout the intervention. Delivery of these nudges will vary from 4 times in the first month, to 2 times in the second and third months, and monthly until the end of the intervention. These motivational nudges will be delivered in different formats, designed to be appealing and engaging (e.g., animated short videos containing simple tips on different forms of breaking sitting time and benefits of that); social support and social modeling will also be enhanced via these nudges (e.g., including testimonials from study participants willing to share their ongoing experience, including photos and short videos using the desk) allowing to support relatedness, perceived competence, and autonomy to use the desk. These are the three basic psychological needs supporting autonomous motivation according to Self-Determination Theory [60]. This type of motivation, in turn, has been shown to allow the integration of new health behaviors in the long term while also enhancing well-being [61].

To determine if the outcomes’ changes observed during the 6 months of work can be maintained in a context without the stimulus (i.e., no sit-stand desk), the intervention group will be followed for 3 months, in which they will be without the sit-stand desks. By the end of the intervention period and at the end of the follow-up, assessments will be conducted, and feedback provided to all participants assuring valuable information regarding participants sedentary patterns, body composition, eating patterns, health and work-related outcomes, fatigue, presenteeism, job satisfaction, well-being, and quality of life, and information on how these have changed over the course of the study.

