### Plans to promote participant retention and complete follow-up {18b}

Assessments will be conducted by the end of the intervention period and at the end of the follow-up. To maximize retention at all assessments we will:Send participants an advance reminder that measurements are upcoming, using a personalized email sent 2 to 3 weeks ahead of the measurement dates, complemented by a phone call to confirm/arrange an appropriate appointment time (suited to participants schedules).Send a confirmation of the date, time, and location (always inside the campus of the university, in a calm and adequate location).Text participant in the previous day leading up to their appointment to remind them about the time, date, and location.

To enhance overall adherence to assessment periods, feedback will be provided at the end, to all participants, assuring valuable personal information regarding participants sedentary patterns, body composition, eating patterns, health and work-related outcomes, fatigue, presenteeism, job satisfaction, well-being, and quality of life, and information on how these have changed over the course of the study. The control group will only receive that feedback on the second evaluation moment, as providing feedback on the baseline can influence their actions during the control phase, which is not desired.

The value, detail, and richness of the information provided via these assessments will be highlighted since the beginning of the study, for example in the dissemination contacts/explanation of the trial, as well as in the initial psychoeducational session. Furthermore, this initial session will highlight the importance of participation in the trial (description of how important RCTs are for science will be embedded in the information provided), and thus, reducing the risk of dropout. The control group (in higher risk of dropping out in the absence of intervention) will also be provided with the opportunity of having the intervention (waiting-list group) after the 6-month assessment period.

During the trial, a website will be nurtured with interesting information (i.e., short films highlighting the evidence-based benefits of sit-stand desk usage; shortcuts highlighting the several phases of the study with the inclusion of the participants (see Intervention description {11a} for more details).

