### Dissemination plans {31a}

The rationale for this project entails novelty and generates new knowledge enough to publish at least 3 scientific papers in international peer-review Journals. (1) protocol publication; (2) main results from the intervention considering the several outcomes; (3) main results from the follow-up phase.

Furthermore, these findings will be initially presented at international and national conferences. Additionally, to disseminate the project on a larger scale, there is a plan to develop four short cut videos depicting the several phases of the project. These videos will be created by the HEI-Lab researchers, along with bachelor and master students from their faculty, and shared with the Lusófona University. The goal is to highlight the chronology of the project, and to stimulate the uptake of this type of intervention by disseminating participants’ experiences as they were shaped by the project: The first clip will show the participants in the baseline assessments. The second video will highlight the initial session. The third clip, released on the fourth month of the project, will focus on the intervention and the new reality of the participants. The fourth clip, released towards the end of the sixth month of intervention, will focus on the main changes the participants feel from a longer use of the sit-stand desks and other aspects not mentioned in the prior video. Finally, a fifth clip will be released in the follow-up period and will feature the study’s main findings and testimonies from the participants, including adaptations made.

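### Desk-use content on an openly linked study website, and clips released around the assessments, create an avoidable risk of contaminating controls at 6 months and influencing behaviour at 9 months

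*Protocol article*

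**What the plan says.** All references are to the protocol article.

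**Control condition.** The abstract (Methods) has controls working as usual "with no contextual change or prompts during the 6-month intervention". Intervention description {11a} names the recipients of the motivational content: "intervention participants will also be provided motivational nudges throughout the intervention".

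**Safeguards.** Sequence generation {16a} randomises by site to limit contamination and keeps together workers who can see each other's workstations. The retention section {18b} withholds baseline feedback from controls, because "providing feedback on the baseline can influence their actions during the control phase, which is not desired".

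**Website.** Study setting {9} describes it as "a tool for disseminating strategies to prompt participants to use the sit-stand desk throughout the intervention". Under {26a} the investigator contacts all potential participants and will "provide the link to the website of the study, so that all doubts can be solved prior to the baseline evaluation moment". Section {11c} refers to intervention content held on the site. Section {18b} has it updated during the trial with "short films highlighting the evidence-based benefits of sit-stand desk usage". Section {31c} names it as a public route to the full protocol. None of these sections states a restriction by arm.

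**Clips.** Under Dissemination plans {31a} the clips are shared with the university, with the stated aim of encouraging uptake through participants' experiences. "The third clip, released on the fourth month of the project, will focus on the intervention and the new reality of the participants". The fourth, late in the sixth month of intervention, covers the changes participants feel. Finally, "a fifth clip will be released in the follow-up period", carrying the main findings and participant testimonies.

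**The concern.** The ongoing motivational content is part of what is meant to differ between the arms. The plan acts on contamination in two places, by randomising sites and by withholding baseline feedback from controls. It then leaves two other routes open, the website and the clips.

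If controls see tips on breaking up sitting and act on them, the arms differ less at M1 and the effect is underestimated. If participants see the study's main findings before or during M2, their behaviour in the follow-up phase may reflect that knowledge as well as the removal of the desk (intervention arm) or its arrival (control arm). The second objective, maintenance without the desk, rests on M2.

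**Working it through.** No arithmetic on effect size applies, because the documents give no exposure or uptake rate. The check is a comparison of audience and dates.

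**Step 1: who can reach the content.** The link goes out before baseline, and randomisation follows baseline ({16a}), so every future control has received it. The site is also a public route to the protocol ({31c}). The same site carries desk-use strategies ({9}), intervention content ({11c}) and benefit films during the trial ({18b}). The article does not say whether individual pages are restricted. Control exposure after randomisation is therefore a likely inference, not a stated fact.

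**Step 2: the calendar.** Trial status gives 1 March 2023 as the start of the intervention. Six months run from March to August, and the three follow-up months from September to November. Outcomes {12} places M1 in the final month of intervention (August) and M2 in the final month of follow-up (November). Section {18a} places them after 6 and after 9 months, which is from about 1 September and 1 December.

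**Step 3: releases against assessments.**

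| Material | Release | Timing under {12} | Timing under {18a} |
|---|---|---|---|
| Website films | During the trial | Able to precede M1 | Able to precede M1 |
| Clip 3 | Month 4 | Before M1 | Before M1 |
| Clip 4 | Late month 6 | Before, during or after a participant's M1 week | Before M1 |
| Clip 5 | Months 7–9, month not fixed | Before M2 if in months 7–8; may overlap M2 in month 9 | Before M2 |

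The month of clip 3 is counted from the start of the project. Counted from the intervention start it is June; counted from the start of recruitment (1 January 2023) it is April. Both precede August, so the order does not depend on the reading.

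**Step 4: can controls act on it without a desk?** In part. Strategies for using the desk are of no use to them before month 6. But the nudges described in {11a} include tips on different ways of interrupting sitting, which need no desk. Sit-to-upright transitions and prolonged sitting are among the primary variables ({12}, {18a}). The device removes reporting error but not real behaviour change, and participants are unblinded after baseline ({17a}). Many secondary outcomes are self-reported.

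**Step 5: direction.** At M1, uptake by controls would pull the contrast towards no difference. At M2 no direction follows: controls then have desks, the intervention arm has none, and either arm could respond to the findings.

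**The case against.** The strongest contrary case has five parts.

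- **Access is inferred.** The link is sent before arms exist, so that doubts can be resolved. The retention section names no audience for the films, and a condensed article may leave access rules to the full protocol. This stands as a limit on certainty. It does not remove the point, because the wide distribution of the link, the public status of the site and the release months are all stated.
- **Much is already shared.** Both arms attend the psychoeducational session ({6b}, {11a}), and the extra effect of a benefit film is unknown. This limits the likely size. One shared session is still not the same as continuing motivational content.
- **The no-prompt wording is in the abstract.** Sections {6b} and {11a} define the control mainly by the absence of a desk. However, {11a} also assigns the nudges to intervention participants, so the intent is consistent.
- **The withheld feedback is personal data**, which differs from general information. The parallel is therefore loose, though the stated reason for withholding it, influence on controls' behaviour, applies to both.
- **M2 is not free of information by design.** Personal feedback is given at the end of the intervention, and prompts are planned after it ({18b}, {30}). This stands, and it is one reason to claim only a risk at M2.

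A reader might also infer more than the text supports:

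- *Testimonies reach controls before M1.* Testimonials are stated only for the intervention-arm nudges and testimonies only for clip 5. Clips 3 and 4 show participants' experience.
- *Findings are certain to be released before M2.* That follows from {18a} but not from {12}.
- *Both comparisons are biased, with a calculable loss of power.* Any such figure would need a leakage rate that the documents do not give.

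**Conclusion.** The point holds as an avoidable design risk. The plan means to keep motivational prompts from controls for 6 months and guards against contamination. It nevertheless places desk-use strategies and benefit films on a website linked to all potential participants and publicly reachable, with no arm restriction stated. It also dates one uptake-promoting clip before M1, one possibly before or during M1 recordings, and a main-findings clip before or during M2.

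The M1 contrast may be diluted and M2 behaviour may be influenced. The size is unknown, and the direction at M2 is unclear. The conclusion assumes that the website content is not restricted by arm in some unshown document and that clips shared with the university reach control staff who work there. Both are plausible, and neither is stated. Because the change is cheap, it is worth making even though bias is not demonstrated.

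**What to change.** 1. Deliver desk-use prompts and benefit films only to the intervention arm, by log-in or direct e-mail, until the last M1 recording is complete. Keep neutral study information on the open page.
2. Hold clips 3 and 4 until all M1 recordings are complete.
3. Hold clip 5, with the main findings and testimonies, until all M2 recordings are complete.
4. State the access rule and these release conditions in {9}, {18b} and {31a}, tied to completion of recordings and not to calendar months. This also removes the dependence on whether {12} or {18a} gives the assessment date.

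The cost is later dissemination and possibly slightly less engaging retention content for controls. The latter deserves a thought, since {18b} regards controls as the arm more likely to drop out. The reminders, the feedback at the second assessment and the promise of a desk after 6 months are unaffected. Trial status says that two assessments were still to come, so on the article's own account the change could still be made.

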### Eligibility criteria {10}

The inclusion criteria for this study comprise working at least 0.6 full-time; being more than 20 years old; and spending at least 70% of a working week performing desk-related activities. Participants will not be able to participate if they already use a sit-stand desk, if they do not have a personal space where a sit-stand desk can be assembled, or if they have musculoskeletal disorders/health conditions, making it impossible to work in a standing posture.

### Who will take informed consent? {26a}

The PI of the study will contact all potential participants for a detailed explanation of the trial, as well as provide the link to the website of the study, so that all doubts can be solved prior to the baseline evaluation moment. On the previous day to the baseline measurement, each potential participant will receive an email with informed consent, allowing access to all the corresponding information in advance. On the next day (baseline assessment), one trained evaluator (i.e., Ph.D. candidate with a Master in Exercise and Health and a certified Exercise Physiologist by the Portuguese Government) will answer any questions prior to the potential participants signing the written informed consent.

### Additional consent provisions for collection and use of participant data and biological specimens {26b}

On the consent form, participants will be asked if they agree to use of their data should they choose to withdraw from the trial. Participants will also be asked for permission for the research team to share relevant data with people from the University taking part in the research or from regulatory authorities, where relevant. This trial does not involve collecting biological specimens for storage.

## Interventions

### Explanation for the choice of comparators {6b}

SUFHA is designed for a sample of adult University office workers and will consist of two groups. A waiting-list control group will only attend a psychoeducational session regarding the independent benefits of reducing and interrupting sitting time with standing, with no contextual change during the 6-month intervention (i.e., no access to the sit/stand desk). The intervention group will attend the psychoeducational session and will be provided with the opportunity to have a sit-stand desk in their workplace, allowing them to work seated or standing and change between these postures as many times as they desire for 6 months.

After the intervention period, the waiting-list control group will have access to the sit-stand desk.

### Intervention description {11a}

SUFHA will be delivered over 6 months, with another 3 months of follow-up. Given the relative lack of literacy concerning the independent effects of SB in health (i.e., most health campaigns have been focused on raising PA levels) [59], both the intervention and control groups will attend an initial psychoeducational session regarding the independent benefits of reducing and interrupting sitting time with standing and other activities. Besides raising information and literacy, this type of strategy (i.e., educational seminar) has been found to facilitate behavior change in a similar setting [50]. The intervention group will be provided the opportunity to work on a sit-stand desk (Vinsetto, Model 923-043) for 6 months, while the control group will remain on a traditional sitting desk. The sit-stand desks allow the employees to choose if they want to work while sitting or standing and change between postures as often as they desire and have been found to be crucial for the aimed behavioral change [50].

As mentioned above, the intervention will comprise an initial session given by a specialist in this area of research (i.e., Assistant Professor in a Sports Science Faculty with a Master in Exercise and Health, a Ph.D. and a Post-doctoral training within the sedentary behavior research area, with over 50 publications in this field and with many years of experience with observational and experimental studies within the Scopus of sedentary behavior) concerning the benefits of reducing sitting time and interrupting it with standing activities, providing information and practical tips on how to reduce sedentary time and use the sit-stand desk. Before the beginning of the intervention and considering the randomization process, a visit will be made to the work site of the participants allocated to the intervention group, to assemble the sit-stand desks, without any associated costs. Desk mounts involve a device that is installed on top of a conventional workplace desk often by means of a clamping arm. The device facilitates regular transitions between sitting and standing postures, predominantly while performing computer-based activities. It can be placed in standing mode via an easy upward pulling motion that lifts the display unit(s) and objects placed on the work surfaces. To enhance desk use, participants will also be given the following: (i) a demonstration of how their sit-stand desk works; (ii) tailored information on the correct ergonomic posture; (iii) and individualized guidance on gradually building up standing time. This information will then be written down on a flyer allowing the participants to read it anytime they feel necessary. Participants will afterward be able to use their sit-stand desk for the following 6 months.

There is evidence that temporary context changes, such as holidays, threaten to derail newfound routines, such as standing more often in the workplace [39]. Furthermore, after the intervention period, participants will no longer have the sit-stand desk. Thus, to enhance motivation and self-regulation for internalizing the new routines of breaking up sitting time, intervention participants will also be provided motivational nudges throughout the intervention. Delivery of these nudges will vary from 4 times in the first month, to 2 times in the second and third months, and monthly until the end of the intervention. These motivational nudges will be delivered in different formats, designed to be appealing and engaging (e.g., animated short videos containing simple tips on different forms of breaking sitting time and benefits of that); social support and social modeling will also be enhanced via these nudges (e.g., including testimonials from study participants willing to share their ongoing experience, including photos and short videos using the desk) allowing to support relatedness, perceived competence, and autonomy to use the desk. These are the three basic psychological needs supporting autonomous motivation according to Self-Determination Theory [60]. This type of motivation, in turn, has been shown to allow the integration of new health behaviors in the long term while also enhancing well-being [61].

To determine if the outcomes’ changes observed during the 6 months of work can be maintained in a context without the stimulus (i.e., no sit-stand desk), the intervention group will be followed for 3 months, in which they will be without the sit-stand desks. By the end of the intervention period and at the end of the follow-up, assessments will be conducted, and feedback provided to all participants assuring valuable information regarding participants sedentary patterns, body composition, eating patterns, health and work-related outcomes, fatigue, presenteeism, job satisfaction, well-being, and quality of life, and information on how these have changed over the course of the study.

